### Phase 3: Intervention Evaluation

We will conduct a pilot hybrid type 1 effectiveness-implementation cluster-randomized controlled trial [20] to assess intervention acceptability and feasibility (clinics: N=4; adolescents: N=120). The cluster-randomized controlled trial design minimizes the risk of contamination among participants in different arms and is ideal when settings are similar in terms of population characteristics. These trials are frequently used when interventions are to be carried out at the level of whole groups. Implementation science hybrid designs assess intervention effectiveness in real-world settings and document barriers and facilitators to delivery and sustainability [20]. Considering that our goal is to disseminate the intervention widely, we must understand the contexts that influence success and failure, so that we can plan for them and mitigate weaknesses accordingly.

We will enroll 120 adolescents across 4 clinics; 2 clinics will be randomized to implement the intervention condition, and 2 clinics will be randomized to a time-attention control. All African American patients unvaccinated for HPV (aged 15-26; all genders) will be approached to enroll in the study when they come in for a visit, regardless of the purpose of that clinical visit. After informed consent is collected from adolescents, we will collect preintervention, immediately postintervention, 2-month postintervention, and 6-month postintervention survey data related to the behavior change objectives -- increased knowledge of vaccines, reduced stigma, and increased motivation, which all result in improved vaccine confidence and higher vaccination rates — in addition to participant demographics and known potential associates of vaccination or vaccine hesitancy. We will collect design metrics to assess feasibility and acceptability, informed by the Bowen framework [27] (Figure 2).

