**Objective:**

In this 30-month study, we propose to develop an in-clinic, youth-tailored, vaccine-promoting intervention for vaccine hesitancy reduction that can be seamlessly integrated into the existing environments of pediatric and family practice settings in rural Alabama.

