### Recruitment

For the first and second phases of the study, participants will be recruited through our health care partner—the University of Alabama at Birmingham Selma Family Medicine clinic—and their local community–based network, which includes high schools and nonprofit agencies. During the third phase, in which the newly crafted intervention will be tested, participants will be recruited in enrolled clinics. Screening for eligibility (eg, vaccine status, age, etc) will occur via self-report and be corroborated via clinical record and immunization registry verification.

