### Medical Records

We propose to collect data on vaccination from medical records at partner clinics. We will request records from partner clinics, and a member of each clinic will extract them for evaluation. The research team will review medical records for evidence that participants accepted vaccination during the 6-month study period, as well as evidence of whether the participants completed the vaccine series.

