### Phase 3: Data Management and Quantitative Analysis

A descriptive analysis of all study feasibility and outcome variables will be summarized by using means and SDs for continuous measures and frequencies and percentages for categorical measures. Between-group differences will be compared by using standard 2-tailed cluster analyses. Further, 2-sample tests for proportions [28] will be used to compare initial vaccination acceptance, the indication of dose completion, and study dropout. An adjusted McNemar test [29] will be used to determine if the intervention group had any changes in vaccine knowledge post intervention. Similar analyses will be used in the control group, and the two groups’ changes will be examined. For any continuous measure (eg, stigma), 2-sample *t* tests [30] will be used, and appropriate assumptions will be validated. Factors related to unexpected design or study implementation issues, such as systematic enrollment issues at clinics or differential times between patients’ first visit and their follow-up resulting from issues beyond common follow-up issues, will be assessed. If it is determined that these issues require analysis adjustment, we will use generalized estimating equations to compare group differences in all measures while adjusting for these factors. Generalized estimating equations require all missing data to be missing completely at random; however, as our primary outcome relates to initial vaccination acceptance, we do not expect any missingness. Likewise, we will assume that study dropout is an indicator of incomplete dosing. Missing values for other outcomes will be examined, and if missingness at random can be assumed, multiple imputations [31] will be used.

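### Youths who came for the HPV vaccine, or had already decided on it, count as acceptances in either arm; record visit purpose and prior intention and adjust for them

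*Protocol article*

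**What the plan says.** The entry rule is in the protocol article, Methods, Phase 3: Intervention Evaluation: HPV-unvaccinated African American patients of any gender, aged 15 to 26, "will be approached to enroll in the study when they come in for a visit, regardless of the purpose of that clinical visit". The Recruitment section adds that "Screening for eligibility (eg, vaccine status, age, etc) will occur via self-report", checked against clinical records and the immunization registry. Hesitancy, intention and reason for attendance are not among the items named, although the list is open-ended.

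On the outcome, Phase 3: Data Management and Quantitative Analysis states that "our primary outcome relates to initial vaccination acceptance". The Medical Records section has the team look for "evidence that participants accepted vaccination during the 6-month study period". A dose given on the day of enrolment is inside that window. Initial acceptance is compared by two-sample tests for proportions, under a general statement that group differences will be examined with cluster analyses. Generalized estimating equations with adjustment are held back for unexpected design or implementation problems that are judged to need them.

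The Abstract's Objective describes a "vaccine-promoting intervention for vaccine hesitancy reduction". Two of the four clinics are randomized to each condition, with 120 youths in total.

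**The concern.** A youth who came in for a first HPV dose meets the entry rule and will very probably accept in either arm. That acceptance says little about whether hesitancy was reduced. Two things are at stake, both confined to the effectiveness signal.

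- **Interpretation.** If such youths are more than a negligible share, the all-comer difference is smaller than the effect on youths who had not already decided. Table 1 of the article lists effect-size estimation as an outcome, so this matters for planning a larger trial.
- **Balance.** With two clinics per arm, randomization cannot be relied on to even out visit mix. A difference between arms, by chance or through recruitment, passes into the comparison of acceptance.

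Mixed visit purposes are the expected result of the entry rule, so an adjustment reserved for unexpected problems does not clearly reach them.

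**Working it through.** The article gives no effect size, power or share of vaccine-seeking visits, so there is no figure of its own to reproduce.

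**Inputs from the article:** 120 youths and 4 clinics, 2 per arm. If equal, 120/2 = 60 per arm and 120/4 = 30 per clinic. Alabama HPV series completion is about 20% (Background), used only as a guide to a base rate.

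**Assumed inputs:** f, the share attending for the HPV vaccine (5% to 30%); s, acceptance among them (95% or 100%, the same in both arms); p0 and p1, acceptance among the others in the control and intervention arms.

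**Step 1: effect in all enrolled youths.** The acceptance rate in an arm is f·s + (1-f)·p. With the same f and s in both arms, the difference is (1-f)(p1 - p0), whatever s is. With p0 = 20%, p1 = 40%, s = 100%, 60 per arm, two-sided 5% and no clustering:

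| f | Control | Intervention | Difference | Power | Vaccine-seekers among control acceptances |
|---|---|---|---|---|---|
| 0% | 20% | 40% | 20 points | 67% | 0% |
| 5% | 24% | 43% | 19 points | 60% | 5/24 = 21% |
| 10% | 28% | 46% | 18 points | 53% | 10/28 = 36% |
| 20% | 36% | 52% | 16 points | 42% | 20/36 = 56% |
| 30% | 44% | 58% | 14 points | 33% | 30/44 = 68% |

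For an assumed 15-point effect the differences are 15 × 0.95 = 14.25, 15 × 0.90 = 13.5 and 15 × 0.80 = 12.0 points at f = 5%, 10% and 20%.

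**Step 2: unequal visit mix, no true effect.** The false difference is (f in one arm - f in the other) × (s - p0).

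- 10% against 0%, s = 95%, p0 = 20%: 0.10 × 0.75 = 7.5 points. Directly: (0.10 × 0.95 + 0.90 × 0.20) - 0.20 = 0.275 - 0.20 = 0.075.
- 15% against 5%, s = 100%, p0 = 20%: 0.10 × 0.80 = 8 points.

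**Step 3: compare with sampling error.** For 27.5% against 20% with 60 per arm, the standard error is √[(0.275 × 0.725 + 0.20 × 0.80)/60] = √(0.3594/60) = 7.7 points before clustering. The false 7.5 points is about one standard error.

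**Step 4: visit mix varying by clinic.** A simulation used 200,000 runs, 4 clinics of 30, no effect, p0 = 20%, s = 100%, mean f = 10% and a pooled z test that ignores clinic. It rejects in 5.2% of runs with virtually no clinic variation in f, 7.9% with an SD of 5 points and 15.7% with an SD of 10 points. These figures describe a test that ignores clinic and are not the error rate of the article's analysis, which refers to cluster methods.

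**Step 5: what recording visit purpose buys.** In the first case of Step 2, youths not attending for the vaccine accept at 20% in both arms. Comparing like with like returns a difference of 0 instead of 7.5 points.

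**The case against.** The best defence is that all-comer enrolment is deliberate and coherent. This is a pilot hybrid type 1 trial, mainly about acceptability and feasibility, and the eventual users are all unvaccinated youths in the waiting room. The (1-f) factor then gives the true effect in that population. This stands. A reader might infer that the entry rule biases the trial, but the article does not support that.

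A reader might also infer that visit mix drives the arm difference. The article gives no share of vaccine-seeking visits. Its low county vaccination rates, and its remark that adolescents are often ambivalent about preventive care, suggest that the share may be small. At 5% the loss is 1 point in 20, which a pilot of this size could not detect. This also stands: the imbalance is a possibility and has not been demonstrated. Any clinic-level prognostic factor would act in the same way with four clinics.

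The safeguards help only in part. Clinic-level vaccination rates are collected before the start (Effectiveness Data), but they do not describe the visit mix of those enrolled. The preintervention survey covers motivation and known associates of vaccination; visit purpose and intention are not named, and the questionnaire is not shown. Systematic enrolment issues at clinics can trigger adjustment, but only conditionally.

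Finally, an article may leave covariates and supportive analyses to the full protocol or SAP. That answers a complaint of omission. It does not answer the stated combination of enrolment at any visit and adjustment only for the unexpected.

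**Conclusion.** The point holds in a limited form. The article's rules let youths who had already decided count as acceptances in either arm, and its stated comparison does not take this into account unless an unexpected problem is declared. Under assumed shares of 5% to 20%, the all-comer difference is 5% to 20% smaller than the effect in the remaining youths. A 10-point difference in visit mix between arms could add about 7.5 to 8 points with no true effect. All rates are assumptions, and at a negligible share the point has no practical weight. It also presumes that the primary outcome includes HPV acceptance, since the article does not say which vaccine is meant.

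A reader might conclude that youths booked for HPV vaccination should leave the primary denominator. That does not follow. It would change the population of interest and make the primary analysis depend on how each of four clinics labels its bookings, which could bring back a clinic-level imbalance.

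**What to change.** 1. Keep all-comer enrolment, and keep all enrolled youths as the primary denominator.
2. Before the intervention is delivered, record the purpose of the visit and add one item to the planned survey on existing intention to get the HPV vaccine.
3. Prespecify the intention item as a baseline covariate in a cluster-aware comparison of initial acceptance, in place of adjusting only if unexpected issues arise. Report the adjusted result as a difference in proportions, so that it still describes all enrolled youths.
4. Report a supportive analysis limited to youths whose visit was not for HPV vaccination. This addresses the effect in youths who did not attend for the vaccine; the covariate addresses imbalance.

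The cost is one visit-purpose field, one survey item and a little more analysis. The intention item might itself prompt vaccination, in both arms. Adjustment does not remove the limits of having four clinics; it deals with this one source of difference between them.

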**Figure 2 figure2:**
[figure not shown]
Randomized controlled trial study flow (phase 3).

All participant data collection will occur electronically. Informed consent will be collected via Adobe Sign (Adobe Inc), and self-report data will be collected through a standardized Qualtrics (Qualtrics International Inc) survey. Pre- and postintervention data collection, which will occur in clinics, will be conducted with iPads (Apple Inc) that are dedicated to the study site. Data will be immediately uploaded to a secure database through wireless connectivity. Self-report data to be collected at 2 and 6 months post intervention will be captured by using the same standardized Qualtrics survey that will be used in clinics; the direct survey link will be shared via text or email, depending on the participants’ preferences.

We will conduct exit interviews with clinic health providers to assess barriers and facilitators to implementation specifically to inform regional dissemination.

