### Feasibility Data (The Bowen Model [27])

Clinic staff will maintain logs on acceptances and refusals to study participation. We will use these data to assess if the study procedures and protocols are feasible and the intervention is acceptable (Table 1).

**Table 1 table1:** Components of the Bowen model [27].

Component	Assessment focus	Sample outcomes
Demand	Documenting the use of the intervention	Fit within organizational culture and perceived effects and demand
Acceptability	Health providers’ and patients’ reactions to the intervention	Satisfaction, intent to continue use, and perceived appropriateness
Implementation	Extent to which the intervention is implemented as planned	Degree of execution and resources for implementation
Practicality	Extent to which intervention can be implemented in rural Alabama	Cost analysis factors affecting implementation
Adaptation	Modifications needed to accommodate the context	Degree to which outcomes are obtained with the mobile format
Integration	Level of system change for integrating the intervention	Perceived fit with infrastructure and perceived sustainability
Expansion	Potential success of the intervention in a different setting	Fit with the local goals and culture
Limited efficacy testing	Small-scale implementation	Effect size estimation and effects on key intermediate variables

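### Youths are very probably recruited after their clinic's allocation, with no masked or arm-neutral invitation described, and the default test of vaccination acceptance is unadjusted for baseline hesitancy

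*Protocol article*

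**What the plan says.** Phase 3: Intervention Evaluation fixes the allocation at clinic level: "2 clinics will be randomized to implement the intervention condition, and 2 clinics will be randomized to a time-attention control". It sets the number of participants ("We will enroll 120 adolescents across 4 clinics") and says that all eligible HPV-unvaccinated patients "will be approached to enroll in the study when they come in for a visit, regardless of the purpose of that clinical visit". The Recruitment section places this on site: "participants will be recruited in enrolled clinics".

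Consent is individual and comes before any survey: "After informed consent is collected from adolescents, we will collect preintervention, immediately postintervention, 2-month postintervention, and 6-month postintervention survey data". The text after Figure 2 adds the location: "Pre- and postintervention data collection, which will occur in clinics". The baseline survey covers knowledge, stigma, motivation and known correlates of vaccination or hesitancy.

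Under Feasibility Data, "Clinic staff will maintain logs on acceptances and refusals to study participation", and the stated use of these logs is to judge feasibility and acceptability.

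Under Phase 3: Data Management and Quantitative Analysis, the primary outcome relates to initial vaccination acceptance, compared by a 2-sample test for proportions. GEE adjustment is held in reserve for unexpected design or implementation problems, of which systematic enrollment issues at clinics are one example. Effectiveness Data adds clinic-level vaccination rates, collected before the study and yearly.

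**The concern.** In a cluster trial, randomizing clinics balances clinics (in expectation), not the people who later agree to take part. When individuals are identified and consented after their clinic's allocation, the invitation can differ between arms, and so can the mix of people who accept it.

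This trial is exposed because the likely selection variable is vaccine hesitancy, which the intervention targets and which strongly determines the outcome. If hesitant youths decline more often where they are offered vaccine counseling than where they are offered a time-attention control, the intervention arm starts out more willing to vaccinate. The reverse pattern would hide a real benefit.

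The trial is a pilot, so the harm would fall mainly on the signal of effectiveness and on the effect-size estimation listed in Table 1. Those would inform any later trial.

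**Working it through.** **Order of events.** The article does not date the randomization, and Figure 2 is not shown. Clinics are randomized to implement a condition. Patients are approached visit by visit in those clinics, and the surveys immediately before and after the intervention are done there. A clinic delivering its condition while it enrolls must know that condition for nearly all of its recruits. Recruitment after allocation is thus a strong inference about staff. Whether youths know the arm when they decide is not stated.

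**No figure to reproduce.** The article gives no expected acceptance rate, participation rate, power or intracluster correlation. Everything below is an assumption, with its range.

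**Model, with no true effect.** Youths are receptive (share r, acceptance a_r, participation 90%) or hesitant (share 1 − r, acceptance a_h, participation h). Then:
- receptive share among those enrolled: s = 0.9r / [0.9r + (1 − r)h]
- acceptance among those enrolled: s·a_r + (1 − s)·a_h

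**Worked example:** r = 30%, a_r = 40%, a_h = 5%.
- Control, h = 80%: s = 0.27 / (0.27 + 0.56) = 32.5%; acceptance = 0.325 × 40% + 0.675 × 5% = 16.4%.
- Intervention, h = 50%: s = 0.27 / (0.27 + 0.35) = 43.5%; acceptance = 0.435 × 40% + 0.565 × 5% = 20.2%.
- Spurious difference: (0.4355 − 0.3253) × 35 points = 3.9 points. Exchanging the two participation rates gives −3.9 points.

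**Range:** r from 20% to 40%, a_r 40% or 50%, a_h 5% or 10%, control h = 80%.

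| Hesitant participation, intervention clinics | Spurious difference (points) |
|---|---|
| 70% | 0.7 to 1.5 |
| 60% | 1.6 to 3.2 |
| 50% | 2.7 to 5.3 |

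**Against sampling error.** Assume 60 per arm (an equal split, not stated) and ignore clustering. The standard error in the worked example is √(0.202 × 0.798/60 + 0.164 × 0.836/60) = 7.1 points, and the 95% half-width is 1.96 × 7.1 ≈ 14 points. Clustering would be expected to widen this.

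**What the log would show.** In the example, overall participation is 0.27 + 0.56 = 83% in control and 0.27 + 0.35 = 62% in intervention clinics. A log of acceptances and refusals would reveal that gap, but not that the extra refusals were hesitant youths. Nor does such a log by itself give the number eligible: 60 acceptances and 15 refusals read as 80%, whether 80, 100 or 150 youths were eligible (75%, 60% or 40% enrolled).

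**What adjustment would do.** Within each type the two arms have the same acceptance (40% and 40%; 5% and 5%), so the difference conditional on type is 0. Adjustment for a good measure of hesitancy removes the artifact in this model; a poor measure removes only part of it.

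**The case against.** The strongest reply has four parts.

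- **The premise is inferred.** Nothing says who approaches patients, whether they are masked or what the invitation says. A time-attention control may leave youths unaware of their arm, and both arms recruit HPV-unvaccinated youths and answer vaccine-related surveys. A reader might infer that everyone knows the arm before consenting. The documents do not support that; they support only that clinic staff very probably know.
- **Safeguards exist.** All eligible patients are to be approached, enrollment issues will be assessed with GEE available, relevant baseline measures are collected, and clinic-level rates do not depend on who consents. These have partial value. However, approaching everyone does not equalize refusal, the GEE is conditional on a later judgment that a problem needs adjustment, and the clinic-level rates are not tied to the primary comparison.
- **The log may hold more.** A reader might infer that it records acceptances and refusals and nothing else. The article's one sentence does not say so, and log columns are detail that an article leaves to the full protocol. That objection stands, so log content is only a supporting check here.
- **The bias is small for a pilot.** That also stands: 1 to 5 points lies well inside sampling error. A larger figure can be produced. If willing youths accept at 50% and hesitant youths at 10%, and 60% of intervention enrollees are willing against 30% in control, the gap is (0.60 − 0.30) × 40 = 12 points. But with 30% willing among those eligible and 90% participation otherwise, hesitant participation in intervention clinics must then fall to (0.27/0.60 − 0.27)/0.70 = 26%. Overall participation would be 45% against 90%, which the logs would make obvious. Nothing in the article suggests so large a gap.

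**Conclusion.** The point holds as a correctable weakness in the stated procedure and default analysis. Recruitment very probably follows allocation, no masked or arm-neutral approach is described, and the primary comparison is unadjusted although suitable baseline measures will be at hand.

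The size and direction of any bias are unknown. About 1 to 5 points is an illustration resting wholly on assumed receptive shares, acceptance rates and participation rates. It models differential refusal, not failure to approach. The documents do not show that selection will occur or that the result would be invalid. The case for acting is that sampling error is visible in a confidence interval while this bias is not, and that reducing it costs little.

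**What to change.** 1. Use the same arm-neutral invitation and consent wording in all 4 clinics, and reveal the condition only after the pre-intervention survey is submitted. This acts on the cause.
2. Prespecify adjustment of the vaccination comparison for pre-intervention hesitancy and motivation, instead of leaving adjustment conditional, and show these measures by arm. The data are already collected.
3. As a supporting check, report participation by clinic and arm from the existing logs, with the number of eligible attenders as denominator where records allow. Eligibility is already checked against clinical records and the immunization registry.

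The cost is revised invitation and consent wording, slightly more logging by clinic staff, one descriptive table and one prespecified model. Adjustment cannot remove unmeasured differences and is limited by having 4 clinics, so the first step matters most.
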